#### Statistical analysis plan

For neuroimaging outcomes (Aim 1), linear and generalized linear mixed-effect regression models will be fit using data from the MRI scans at 0–1, 6, and 24 months to compare trajectories of brain development measures (e.g., cortical and deep cerebral gray matter volumes) over time in infants with and without opioid exposure, controlling for study site and child and family characteristics. The test of a time-by-exposure status interaction will allow us to determine if trajectories over time differ between exposed and unexposed infants. The model will be selected based on the type of outcome with linear models for normally distributed continuous outcomes and generalized linear models for categorical or non-normally distributed continuous outcomes. In addition to the comparisons by the dichotomous opioid exposure variable (i.e., exposed versus unexposed), similar models will examine the impact of the level of opioid exposure on neuroimaging outcomes.

For neurodevelopmental and behavioral outcomes (Aim 2), linear mixed-effect models will be used for continuous outcomes (e.g., Bayley scores) and generalized linear mixed-effect models for categorical outcomes (e.g., presence of a diagnosis), accounting for study site and infant and family characteristics. These models allow us to statistically account for clustering of subjects within study sites. In addition, for outcomes where measurement error is likely to occur, such as different domains of behavioral assessments, latent variable approaches (i.e., structural equation modeling) will allow us to combine more than one measure into a single underlying latent variable to reduce measurement error in models. These models permit testing of hypotheses that, compared with unexposed controls, children with opioid exposure are more likely to have low cognitive scores, demonstrate increased motor abnormalities, and have more behavioral problems, controlling for other possible contributing factors (e.g., other antenatal exposures, postnatal environment, demographics). Sensitivity analyses will be conducted to examine the impact of including subjects with other antenatal exposures in the models.

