**Fig. 2 Fig2:**
[figure not shown]
Conceptual Framework of the ACT NOW OBOE Study. Conceptual framework of the relationships between exposures, effect modifiers, and outcomes.

Missing data are possible for any longitudinal study and are a special cause of concern for the population to be enrolled in this study. We will closely monitor attrition and conduct logistic regression models to compare the characteristics (e.g., opioid exposure, site, maternal and family characteristics) of subjects who remain in the study at 2 years versus those who dropped out to determine if data are missing at random. Patterns of item-level missing data will be examined to determine if particular types of questions (e.g., questions related to maternal drug use) have greater levels of missing data or have missing data rates that differ across groups, suggesting that they may not be reliable. The impact of missing data of both types will be minimized through use of appropriate likelihood-based estimators.^51–53^ These methods yield unbiased estimates and accurate standard errors without sacrificing cases (and thus maximizing statistical power) when data are missing completely at random or predicted by other variables in a given model but independent of the potential values of the outcome itself (i.e., missing at random). If subjects do not appear to be missing at random, we will use pattern mixture models to account for the informative attrition.^54^

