#### Sample size and power estimates

Given the paucity of definitive studies on effects of antenatal opioid exposure to 2 years, power calculations reflect a scientifically meaningful effect size of half a standard deviation unit for a longitudinal outcome based on a sample size of 300 (200 exposed infants and 100 unexposed infants). We assumed three repeated measures (0–1, 6, 24 months), with 80% follow-up at 24 months, a conservative intra-cluster correlation of 0.5 for repeated measures, and a two-sided test with a conservative Type 1 error of 0.01 in recognition of the multiple aims specified for our analysis.

With a sample size of 300, the study will have statistical power of 99% to detect effects this size (*d* = 0.5) with statistical significance. A smaller effect size of a third of a standard deviation (*d* = 0.33) is still detectable with 98% power. Power will be lower but respectable to detect meaningful differences in binary outcomes. Using the proportion of head circumference below the 10th percentile as an example, under the same assumptions, shows that for a control group proportion of 10%, there is 82% power to detect proportions in excess of 25% in the opioid-exposed group (relative risk of 2.5 or higher).

The cross-sectional analyses have lower but still respectable power, especially for continuous outcomes such as the 24-month Bayley cognitive score. As before, for a scientifically meaningful effect size of half a standard deviation unit, based on the sample size of 300 with 80% follow-up at 24 months, a conservative two-sided test at Type I error of 0.01 has 85% power to detect effects of this size with statistical significance. Not surprisingly, only large effects of antenatal opioid exposure (relative risk of 3.7 or higher) are detectable for binary outcomes with low (5%) prevalence in the control/unexposed infants.

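### Comparing observed characteristics of completers and dropouts cannot show whether data are missing at random, so it should not decide whether the pattern-mixture analysis is run

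*Protocol article*

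**What the plan says.** All of this is in the protocol article, in the missing-data paragraph of the Statistical analysis plan section (after Fig. 2), unless stated otherwise.

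- **Diagnostic.** The plan fits "logistic regression models to compare the characteristics (e.g., opioid exposure, site, maternal and family characteristics"). The predictors are listed as examples, and every one of them is an observed variable.
- **Purpose of the diagnostic.** The regression sets against each other "subjects who remain in the study at 2 years versus those who dropped out to determine if data are missing at random".
- **Trigger.** "If subjects do not appear to be missing at random, we will use pattern mixture models to account for the informative attrition".
- **Default analysis.** "The impact of missing data of both types will be minimized through use of appropriate likelihood-based estimators". The plan says these are unbiased under MCAR, or when missingness is "predicted by other variables in a given model but independent of the potential values of the outcome itself (i.e., missing at random").
- **Item-level check.** "Patterns of item-level missing data will be examined to determine if particular types of questions" are missing more often or differ between groups. This concerns the reliability of items and also uses observed data only.
- **Outcome models** (start of the same section). The imaging models compare exposure groups "controlling for study site and child and family characteristics". The neurodevelopmental models likewise account for site and for infant and family characteristics.

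The sample size section plans for 80% follow-up at 24 months. The only sensitivity analysis that the article makes unconditional concerns other antenatal exposures, not missing data.

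**The concern.** The regression is given a job that it cannot do. Its predictors are recorded characteristics, and most of them are of the kind that the outcome models already contain. If they differ between completers and dropouts, the data are not MCAR, but they may well be MAR, the case in which the plan relies on likelihood estimation. What separates MAR from MNAR is whether dropout depends on the 24-month value that nobody saw, and that value is not in the regression.

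The only analysis named for informative attrition depends on this result. Suppose exposed infants who are doing poorly leave for reasons that the recorded characteristics do not capture. The comparison can then look reassuring, the pattern-mixture analysis is not called for, and an attenuated exposure effect is reported. The plan itself singles out attrition as a worry in this population.

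**Working it through.** **1. The logic, from the plan's own definition.** Let R be dropout, X the observed variables in the outcome model (exposure, site, family characteristics) and Y the unseen 24-month outcome.

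| Mechanism | Dropout depends on | Regression of R on X | Likelihood analysis given X |
|---|---|---|---|
| MCAR | nothing | no association | valid |
| MAR | X | association | valid |
| MNAR | Y, given X | may show none | biased in general |

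An association separates the first row from the second. Its absence does not exclude the third. Its presence does not establish the third either: if informative dropout also tracks X, the regression shows the same association as under MAR.

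**2. Inputs from the document.** The plan has a "sample size of 300 (200 exposed infants and 100 unexposed infants"), 80% follow-up at 24 months, an effect of 0.5 SD, a two-sided alpha of 0.01 and a correlation of 0.5 between repeated measures. The plan gives no figure for the missing-data rule itself. As a check on the inputs, equal 20% loss leaves 160 exposed and 80 unexposed infants:

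- noncentrality = 0.5 / √(1/80 + 1/160) = 3.65
- power (normal) = Φ(3.65 − 2.576) = 0.859; with the t distribution, 0.853

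This agrees with the 85% stated for the cross-sectional 24-month analysis.

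**3. Assumptions not in the document.**

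- Outcome: Y = −0.50·exposed + 0.3·X + e, with e of SD 1 and X one family covariate.
- Dropout: logit P(dropout) = a − ln(OR)·z. Here z is X (MAR) or the unseen residual e (MNAR), and a is set to give about 20% loss in each group.
- Trigger: likelihood-ratio test of dropout on exposure, site and X at 5%.

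**4. Results for an outcome measured only at 24 months (true effect −0.50).**

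| Mechanism | OR per SD | Trigger fires | Adjusted estimate |
|---|---|---|---|
| MAR through X | 2 | 94% | −0.50 |
| MNAR, exposed only | 1.25 | about 5% | −0.46 |
| MNAR, exposed only | 1.5 | about 5% | −0.41 |
| MNAR, exposed only | 2 | about 5% | −0.37 |
| MNAR, exposed only | 3 | about 5% | −0.32 |

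The share of the effect lost runs from (0.50 − 0.46)/0.50 = 8% to (0.50 − 0.32)/0.50 = 36%. A firing rate of about 5% is simply the false-positive rate of the assumed test.

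**5. Outcomes with earlier measures.** In a separate run of 1,000 cohorts per setting, two earlier measures entered the likelihood. The exposed-only MNAR estimates at odds ratios 1.25, 1.5, 2 and 3 were −0.47, −0.45, −0.41 and −0.38. The loss is then (0.50 − 0.47)/0.50 = 6% to (0.50 − 0.38)/0.50 = 24%. This applies to the imaging outcomes, scanned at 0–1, 6 and 24 months. By Table 1, Bayley-4 and the vision screen are given only at 24 months, so they have no earlier score on the same instrument.

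**6. Same mechanism in both groups.** With equal outcome-dependent dropout in exposed and unexposed infants, the estimate stays at about −0.50.

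**The case against.** The best defence is that the article fixes no automatic rule. It names no test, alpha or threshold, and speaks only of how the data appear. The paragraph defines MAR correctly, and an analyst who holds to that definition need not read a covariate difference as a departure from it. The sentence may simply blur MCAR and MAR.

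Part of this stands. A reader might infer that the plan switches to pattern-mixture models in exactly the wrong cases, with the firing rates above. The document does not support that: the 5% test, and hence the 94% and 5%, are assumptions made to illustrate the problem. What does not fall away is that the regression is the only diagnostic named for the decision, and no judgement from observed data separates MAR from MNAR.

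A reader might also infer that a fixed share of the effect, such as a quarter, will be lost. That share is one point in a range that runs from about nil to 36%, and it depends on how strongly and in which group unseen outcomes drive dropout. Earlier measures recover part of the loss for imaging outcomes.

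Finally, a reader might infer that there will be no MNAR sensitivity analysis at all. The article does not say so; an unseen analysis plan may add one. The finding is confined to the condition that the article does state.

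**Conclusion.** Wrong as written; it should be fixed. The comparison can reject MCAR and identify predictors of dropout. It cannot determine whether data are MAR, and making the pattern-mixture analysis depend on it contradicts the paragraph's own definition. That conclusion is one of logic and needs no simulation.

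The practical size does rest on the assumptions listed in the working. With MNAR dropout in the exposed group only, the attenuation is 8% to 36% for a 24-month-only outcome and 6% to 24% with two earlier measures. It is about nil if the same dropout acts in both groups. In the exposed-only runs the assumed trigger gave no warning beyond its false-positive rate.

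This is not a fatal defect. A likelihood analysis under MAR is a standard main analysis and is not itself at fault, and an unneeded trigger costs only an extra analysis. The harm lies in false reassurance when the comparison shows nothing.

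**What to change.** - Describe the dropout regression as a check of MCAR and a way to find predictors of dropout, and include those predictors in the MAR model.
- State MAR as the assumption of the main likelihood analysis, not as something that the data will establish.
- Remove the condition on the pattern-mixture analysis. Run it (for example with a delta adjustment of the unseen 24-month outcome) as a pre-specified sensitivity analysis whatever the regression shows. Let the shift differ between exposed and unexposed dropouts, since differential dropout is what produced bias here.
- Choose the range of shifts in advance, and report the shift at which the conclusion changes. Bayley-4 and the other 24-month-only outcomes should be covered explicitly.

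The cost is a change of wording and one extra sensitivity analysis. No new data are needed.

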#### Sample size and power estimates

Given the paucity of definitive studies on effects of antenatal opioid exposure to 2 years, power calculations reflect a scientifically meaningful effect size of half a standard deviation unit for a longitudinal outcome based on a sample size of 300 (200 exposed infants and 100 unexposed infants). We assumed three repeated measures (0–1, 6, 24 months), with 80% follow-up at 24 months, a conservative intra-cluster correlation of 0.5 for repeated measures, and a two-sided test with a conservative Type 1 error of 0.01 in recognition of the multiple aims specified for our analysis.

With a sample size of 300, the study will have statistical power of 99% to detect effects this size (*d* = 0.5) with statistical significance. A smaller effect size of a third of a standard deviation (*d* = 0.33) is still detectable with 98% power. Power will be lower but respectable to detect meaningful differences in binary outcomes. Using the proportion of head circumference below the 10th percentile as an example, under the same assumptions, shows that for a control group proportion of 10%, there is 82% power to detect proportions in excess of 25% in the opioid-exposed group (relative risk of 2.5 or higher).

The cross-sectional analyses have lower but still respectable power, especially for continuous outcomes such as the 24-month Bayley cognitive score. As before, for a scientifically meaningful effect size of half a standard deviation unit, based on the sample size of 300 with 80% follow-up at 24 months, a conservative two-sided test at Type I error of 0.01 has 85% power to detect effects of this size with statistical significance. Not surprisingly, only large effects of antenatal opioid exposure (relative risk of 3.7 or higher) are detectable for binary outcomes with low (5%) prevalence in the control/unexposed infants.

## Discussion

The ACT NOW OBOE Study is a longitudinal cohort study designed to prospectively examine the neurodevelopmental, behavioral, and social/family/home outcomes of infants exposed to opioids in utero and controls. We are currently recruiting exposed and control infants at all four clinical sites and will provide important information on the impact of prenatal opioid exposure on the trajectory of brain development over the first 2 years of life.

### Impact of opioid exposure on the brain

Previous studies suggest that prenatal opioid exposure affects brain development. A small study of opioid-exposed infants (*n* = 29) and controls (*n* = 42) having MRI scans before 2 months of age found that exposed infants had significantly smaller relative volumes of deep gray matter, insular white matter, thalamic ventrolateral nuclei, subthalamic nuclei, brainstem, and cerebrospinal fluid and larger volumes of right cingulate gyrus white matter and left occipital lobe white matter as compared to unexposed infants.^10^ These volumetric changes appear to persist throughout childhood. Compared to individuals without prenatal exposure, quantitative MRIs in adolescents who were drug-exposed demonstrated smaller neuroanatomical volumes, cortical surface areas, and thinner cortices.^7^ In another small study,^55^ a significant proportion (40%) of opioid-exposed infants were found to have punctate white matter lesions or white matter signal abnormality on MRI before 2 months of age, suggesting that opioid exposure is related to aberrant white matter development or even injury. Opioid exposure has also been associated with altered structural (as measured by DTI)^11^ and functional (as measured by resting-state functional connectivity MRI) connectivity.^12,13^ However, all previous studies in this area have been small and have not included well-matched control groups, underscoring the importance of the OBOE study.

### Impact of opioid exposure on development, behavior, and vision

Prenatal opioid exposure may affect later development, behavior, and vision. Several recent reviews and meta-analyses have concluded that infants exposed to opioids in utero are at higher risk of cognitive, language, and visual delays and behavior problems.^56–61^ However, most of these articles have concluded that these findings may be the result of bias in the populations studied and poor quality studies, with particular imbalances in the rate of tobacco exposure in opioid-exposed children versus controls.^56^ The OBOE study should overcome some of these limitations of prior research by including a control group prospectively recruited from the same birth hospitals as the exposed infants, with the inclusion of infants with prenatal nicotine exposure in the control group. The rigorous measures of neurodevelopment including the Bayley Scales of Infant Development, fourth edition conducted by certified examiners and prospective vision screening at age 2 years will also overcome limitations in rigor of prior research.

### Role of parenting and the home environment

Several studies have shown that after controlling for social–environmental and socioeconomic variables, the impact of in utero exposure to various substances on developmental and behavioral outcomes is no longer significant. When examining the outcomes of preschool children with antenatal cocaine exposure, the quality of the caregiving environment was the strongest independent predictor of all outcomes.^62^ Early research examining opioid exposure specifically demonstrated that controlling for social–environmental risk factors such as lower maternal education, low SES, and poor maternal–infant interactions eliminated the significant impact of early exposure on cognitive development.^63^ Furthermore, in the large-scale Maternal Lifestyles Study, the effects of opioid exposure on motor development were no longer significant after controlling for covariates such as SES and quality of the home environment in children through 3 years of age.^64^ The OBOE study was designed to collect extensive information on caregiver IQ (WASI-II), the home environment (HOME Inventory), parenting (MPAQ, HOME), maternal stress/depression/anxiety (PSI-4, PROMIS measures), and social determinants of health (demographic questionnaires).

## Conclusions

With the current opioid crisis in the U.S. and the increasing number of infants with NOWS, more information is needed on the longer-term outcomes of antenatal opioid exposure. The OBOE study will address limitations of prior research to further scientific knowledge of the effects of antenatal opioid exposure on infant brain development and neurodevelopmental outcomes through the use of serial neuroimaging and comprehensive assessments. The study findings can inform legislators and policy makers in decision-making on health policies, interventions, and resources needed to support the development of children born with antenatal opioid exposure.

## Data Availability

Upon completion of the study, data will be available through the NICHD Data and Specimen Hub (DASH).
